Despite this, existing retrospective cohorts mainly focus on all middle/low advanced rectal cancer patients, not the specific individuals with suspicion of LLN metastases. And those results indicate almost no differences in local recurrence and overall survival, except for longer operation time, more blood loss, and more perioperative complications for LLND [7–9, 18]. A Korean report enrolled 900 advanced rectal cancer patients with preoperative swollen LLNs, which showed that the recurrence rate was associated with the diameter of the LLNs [16]. However, there is no strict prospective randomized controlled study on the comparison of TME + LLND and TME for low rectal cancer with suspicion of LLN metastases after nCRT. Thus, the objective of this study is to assess the efficacy and safety of LLND for low rectal cancer patients with suspicion of LLN metastases (TME + LLND versus TME). Furthermore, the risk factors (such as radiologic factors, pathologic factors, and serum protein) to predict local recurrence and overall survival will be further investigated.

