### Study population

The inclusion and exclusion criteria of our trial are shown in Table 1. All eligible patients will strictly comply with the criteria.

**Table 1 Tab1:** The inclusion and exclusion criteria

Inclusion criteria:
•Age (years): 18–75
•Histologically confirmed rectal cancer
•Clinical stage: cTxN1-2M0 or cT3-4N0M0
•Suspicion of LLN metastasis: short-axis diameter of lateral lymph nodes (LLN) >5 mm; short diameter of common iliac or external iliac lymph nodes >6 mm [16, 24, 25]
•No extramesorectal lymph node swelling (short-axis diameter <10 mm)
•No invasion of other organs
•Performance Status (PS): 0, 1
•No past history of chemotherapy, pelvic surgery, or radiation
•Written informed consent operative criteria:
•Mesorectal excision is performed
•Operative findings:
Main lesion of the tumor is located at the rectum
Lower tumor margin is below the peritoneal reflection
Stage R0 after resection
Exclusion criteria:
•High rectal cancer: lower tumor margin is above the peritoneal reflection
•Multiple-cancer patients
•Pregnant patients
•Patients with psychological disorder
•Steroid administration
•Cardiac infarction within previous 6 months
•Severe pulmonary emphysema and/or pulmonary fibrosis
•Physician’s decision to exclude
•Patients with confirmed LLN metastasis: short-axis diameter of LLN >10 mm and a lymph node with an irregular edge, heterogeneous signal, or obvious enlargement and after nCRT has been completed, lymph node enlarges more than 30%
•Emergency surgery
•Patients with coagulopathies

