### Sample size and statistical analysis

Our trial aims to demonstrate that LLND could decrease the 3-year local recurrence rate of low rectal cancer patients with suspicion of LLN metastases. Based on previous studies, we assume that the 3-year local recurrence rate for patients with suspicion of LLN metastases who do not undergo LLND is 15% [13–16], and LLND is expected to show a reduction of 7 percentage points. G*Power 3.1 is used to calculate the sample size. A statistical power of 0.80 and a significance level of 0.05 are chosen, and we assume that there will be a 10% dropout rate. Therefore, 512 patients are needed in this specific trial (256 patients in each group).

All participants in this trial will be analyzed using the intention-to-treat analysis. The chi-square test and Student’ *t* test will be used to compare categorical data and continuous data for the two groups, respectively. The 3-year local recurrence rate, the primary endpoint of this trial, will be analyzed using the Kaplan-Meier method, as well as OS and DFS. In addition, based on different characteristics (such as age, sex, tumor stages, etc.), which can identify the influence of competing risk factors, the Cox proportional hazards (PH) regression model will be tested if Schoenfeld Residuals Analysis confirms PH assumption validation. Otherwise, an alternative extended Cox PH model will be used. SPSS 21.0 (SPSS Inc., Chicago, IL, USA) will be used for all statistical analyses, and a *P* value < 0.05 is considered significant.

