## Discussion

Currently, the hot issue of the treatment of LLN in advanced rectal cancer patients is still being debated in different regions. Eastern countries, especially Japan, favor LLND following TME; however, Western countries believe that nCRT and TME is recommended, and LLDN is added only when a LLN is preoperatively diagnosed as metastatic. Actually, preoperatively enlarged LLNs are not common and only a small proportion of LLDs with a maximum short-axis diameter ≥10 mm, or with a spiculated or indistinct border, or a mottled heterogenic pattern are diagnosed as metastatic [23]. The remaining large proportion of LLNs are underdiagnosed as being metastatic and often confuse surgeons’ treatment strategy. Thus, our trial pays particular attention to this stratification of suspicious LLNs, assessing the efficacy and safety of the LLND in advanced rectal cancer patients.

Another issue we have considered in our trial is the randomization time. In our trial, we randomly allocated participants before nCRT rather than after nCRT. Because LLN metastases are commonly diagnosed before nCRT by their features on pelvic MRI or CT and when chemo-radiation has achieved its effect, the treatment-sensitive regions of any enlarged LLNs will have decreased in size which may confuse the randomization if allocation is performed after nCRT.

This trial is the first randomized controlled trial to investigate the role of LLND in reducing local recurrence rates for low advanced rectal cancer patients with suspicion of LLN metastases. If the efficacy of LLND is verified, which reduces the local recurrence rate from 15% to 8%, LLND can be recommended as a new standard strategy for low advanced rectal cancer patients with suspicion of LLN metastases.

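### Adjusting the primary local-recurrence comparison for baseline LLN diameter would be a cheap improvement; the unadjusted comparison is valid

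*Protocol article*

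**What the plan says.** All references are to the Protocol article.

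- **Sample size and statistical analysis.** For the primary endpoint: "The 3-year local recurrence rate, the primary endpoint of this trial, will be analyzed using the Kaplan-Meier method". A Cox model then comes in addition, with characteristics given as "such as age, sex, tumor stages, etc". The list is open. It neither names nor excludes LLN diameter, and it belongs to the additional model.
- **Background.** Of a cited cohort of 900 patients with swollen LLNs it says that "the recurrence rate was associated with the diameter of the LLNs". It gives no strength of association. It also says that radiologic risk factors for local recurrence will be studied.
- **Study population, Table 1.** Entry requires "short-axis diameter of lateral lymph nodes (LLN) >5 mm", with a threshold of 6 mm for common or external iliac nodes. Another criterion refers to a short axis below 10 mm.
- **Randomization and blinding.** Allocation is 1:1 in blocks of 4, and no stratification factor is named.
- **Discussion.** Patients are randomised before chemo-radiation because treatment shrinks the nodes. The diameter measured at entry is therefore a true baseline value.

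**The concern.** LLN diameter is the one baseline measurement that the article itself links to recurrence in patients of this kind. It is recorded for everyone before allocation, and nothing in the described randomisation balances it. The stated primary analysis nevertheless makes no use of it.

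Two things are at stake, both modest. If the arms differ by chance in node size, the unadjusted result carries that difference and readers will question it. And some precision is given up in a trial that has little to spare.

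**Working it through.** **Inputs from the document.** Local recurrence at 3 years is assumed to be 15% without lateral dissection, and "LLND is expected to show a reduction of 7 percentage points", which gives 8%. On error rates: "A statistical power of 0.80 and a significance level of 0.05 are chosen". Sidedness is not stated. Dropout is 10% and the sample size is 512 (256 per arm). After dropout, 256 × 0.9 ≈ 230 per arm.

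**Inputs assumed.** Diameter is uniform on 5-10 mm, roughly the range that eligibility allows. The hazard ratio (HR) per mm is 1.0 to 2.0. Over the full 5 mm these imply a hazard ratio of 1.2⁵ ≈ 2.5, 1.5⁵ ≈ 7.6 or 2.0⁵ = 32, so the top of the range is extreme.

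**Step 1: the plan's own figure.** Pooled two-proportion formula, with mean rate 0.115:

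n = [z_α √(2 × 0.115 × 0.885) + z_β √(0.15 × 0.85 + 0.08 × 0.92)]² / 0.07²

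- One-sided 0.05: (1.645 × 0.4512 + 0.842 × 0.4484)² / 0.0049 ≈ 256 per arm, or 512 in total, before any dropout allowance.
- Two-sided 0.05: (1.960 × 0.4512 + 0.842 × 0.4484)² / 0.0049 ≈ 325 per arm, or 650 in total.

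By this formula, 512 is reached only with a one-sided test and no allowance for the stated dropout. Two-sided power is 0.700 at 256 per arm and 0.654 at 230. This is the baseline for judging what adjustment can add.

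**Step 2: size of a chance imbalance.**

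- SD of a uniform on 5-10 mm: 5/√12 = 1.44 mm.
- SE of the difference in arm means at 256 per arm: 1.44 × √(2/256) ≈ 0.13 mm. An imbalance of 1.96 SE is about 0.25 mm.
- Approximate shift in the unadjusted log-HR: 0.25 × ln(HR per mm).
- Planned effect: HR = ln(0.92)/ln(0.85) = 0.513, so the log-HR is −0.667.

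| HR per mm | Shift in log-HR | Share of planned effect |
|---|---|---|
| 1.2 | 0.05 | 7% |
| 1.5 | 0.10 | 15% |
| 1.8 | 0.15 | 22% |

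For scale, 230 per arm yields about 230 × (0.15 + 0.08) ≈ 53 events, and the SE of the log-HR is √(1/34.5 + 1/18.4) ≈ 0.29. Even an unlucky imbalance shifts the estimate by about half a standard error or less.

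**Step 3: power with and without adjustment.** Simulation of 2,000 trials per setting. Times are exponential and censored at 3 years, with marginal rates held at 15% and 8%. The test is two-sided at 0.05, comparing Cox with arm alone against Cox with arm and diameter.

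| HR per mm | 256 per arm: unadjusted → adjusted | 230 per arm: unadjusted → adjusted |
|---|---|---|
| 1.0 | 0.679 → 0.679 | 0.656 → 0.661 |
| 1.2 | 0.709 → 0.710 | 0.648 → 0.656 |
| 1.5 | 0.691 → 0.711 | 0.657 → 0.674 |
| 2.0 | 0.692 → 0.737 | 0.641 → 0.681 |

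Type I error was 0.043-0.051 unadjusted and 0.043-0.055 adjusted. Simulation error on each power is about √(0.7 × 0.3/2000) ≈ 1 point. A separate run of 1,500 trials per setting at 230 per arm gave gains of 0.8, 0.4, 2.5 and 2.4 points at HR per mm of 1.2, 1.4, 1.6 and 1.8. The stratified log-rank version was not simulated. Grouping diameter into categories would be expected to recover somewhat less of the gain than using it as a continuous covariate.

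**The case against.** The best case on the other side is that nothing here is wrong. Under 1:1 randomisation the unadjusted comparison is valid, and the simulated type I error confirms it. Diameter is not a stratification factor, so the design does not oblige anyone to adjust for it. The association comes from one cited cohort, without a strength, and may be weak within the narrow range that eligibility allows. Average power already reflects chance imbalance, so the two benefits should not be counted twice. A Cox model as primary is not entirely free either: it replaces a comparison of 3-year rates with a conditional hazard ratio, and it relies on proportional hazards, which the article itself plans to check. All of this stands, and it is why the point is an option for improvement only.

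A reader might infer three stronger claims that the document does not support:

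- **That the primary result would be biased or invalid without adjustment.** It would not be.
- **That the trial ignores diameter.** The covariate list is open and radiologic risk factors are to be investigated, so diameter may well enter the additional Cox model. A full analysis plan, not shown here, may name it.
- **That adjustment would cure the power shortfall in step 1.** It would not. The best simulated figures are 0.737 at 256 per arm and 0.681 at 230.

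What survives is narrower. The article does state a method for the primary endpoint, and that method is unadjusted. An open list in an additional model does not change this.

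**Conclusion.** This is a cheap improvement to a valid analysis. Adjusting the primary test for baseline LLN diameter would keep type I error near 5% and guard against chance imbalance in node size. It would add about 0 to 4.5 points of two-sided power, and about 2 points or less for HR per mm up to 1.5. Gains at the lower end cannot be told apart from simulation error. The figures rest on the assumed uniform 5-10 mm distribution, the assumed HR range and proportional hazards. The stated 80% power is not reached at 512 patients with a two-sided test, whether or not diameter is adjusted for.

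**What to change.** In Sample size and statistical analysis, prespecify the primary between-arm test for local recurrence as one of these:

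- a log-rank test stratified by category of baseline LLN short-axis diameter, measured before chemo-radiation, with few categories and cut-points fixed in advance; or
- a Cox model with arm and the largest baseline LLN short-axis diameter, plus clinical stage if wanted.

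Define a single diameter value per patient, because Table 1 sets different thresholds by nodal site. Keep the Kaplan-Meier 3-year rates and their difference as the reported effect, so that the 15% versus 8% target remains interpretable.

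The stratified log-rank test has the advantage that its validity does not depend on proportional hazards. The Cox option yields a conditional hazard ratio and does rely on that assumption.

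The cost is analysis wording only, with no new measurements, visits or patients. Because the assignment is known to participants, surgeons and investigators, the change should be fixed and dated before any outcome is examined by arm. The sample-size figure in step 1 needs its own correction.

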## Discussion

Currently, the hot issue of the treatment of LLN in advanced rectal cancer patients is still being debated in different regions. Eastern countries, especially Japan, favor LLND following TME; however, Western countries believe that nCRT and TME is recommended, and LLDN is added only when a LLN is preoperatively diagnosed as metastatic. Actually, preoperatively enlarged LLNs are not common and only a small proportion of LLDs with a maximum short-axis diameter ≥10 mm, or with a spiculated or indistinct border, or a mottled heterogenic pattern are diagnosed as metastatic [23]. The remaining large proportion of LLNs are underdiagnosed as being metastatic and often confuse surgeons’ treatment strategy. Thus, our trial pays particular attention to this stratification of suspicious LLNs, assessing the efficacy and safety of the LLND in advanced rectal cancer patients.

Another issue we have considered in our trial is the randomization time. In our trial, we randomly allocated participants before nCRT rather than after nCRT. Because LLN metastases are commonly diagnosed before nCRT by their features on pelvic MRI or CT and when chemo-radiation has achieved its effect, the treatment-sensitive regions of any enlarged LLNs will have decreased in size which may confuse the randomization if allocation is performed after nCRT.

This trial is the first randomized controlled trial to investigate the role of LLND in reducing local recurrence rates for low advanced rectal cancer patients with suspicion of LLN metastases. If the efficacy of LLND is verified, which reduces the local recurrence rate from 15% to 8%, LLND can be recommended as a new standard strategy for low advanced rectal cancer patients with suspicion of LLN metastases.

### Trial status

This trial was initiated in May 2016 and is currently enrolling patients.
